### 9.2. The number of subjects planned to be enrolled

Sample size calculation is motivated by the primary endpoint, based on the Physical Component Summary of SF-36 (PCS). We assessed the PCS for somatoform disorders in the general population with a mean value of 45,76 (SD=10.03) (Schmitz and Kruse, German National Health Interview and Examination Survey - Mental Health Supplement (GHS-MHS) 1998, public use file) and, clinically more realistically, with 37 (SD=12.5) in a sample of 186 patients in the University Hospital Heidelberg, treated in the outpatient departments for psychosomatics and orthopaedic chronic pain, comparable to the trial criteria (Henningesen et al. 2005).

In the trial an effect size of 0.5 is assumed, which is based on the following considerations: Clinically important change on the SF-36 PCS (ie what patients regard as important change) has been considered as follows: small change= 2.5; moderate = 4.5 and large = 6.5 (Wiebe et al 2002). In a previous trial of PIT in a functional somatic disorder (Creed et al. 2003), patients who received PIT improved by a mean of 5.5 points on the PCS compared to those receiving usual care, and this was associated with a reduction of median number of days of restricted activity per month from 5 to 0. Therefore, assuming an effect size of 0.50 on the basis of a standard deviation of 12.5 implies a clinically significant, large change of 6.25 in this measure of physical quality of life.

A sample size of 63 in each group will have 80% power to detect an effect size of 0.50 assuming a mean value of 37 in the control group and a known common standard deviation of 12.5 using a two group normal test with a 0.05 two-sided significance level.

This sample size calculation is based on the standard statistic

$$n = 2\sigma^2 / \theta^2 (z_{0.8} - z_{0.025})^2 \approx 63,$$

where  $\sigma^2 = 12.5^2$ ,  $\theta = 6.25$ ,  $z_{0.8} = 0.84$ ,  $z_{0.025} = -1.96$  and effect size is  $\theta/\sigma$ .

Several scenarios are considered for the number of patients per group. Table 1 shows a deterministic sensitivity analysis for different values of effect size. On the bases of the above requirements the sample size of  $n = 63$  per group was determined. Although, the sample size is very sensible to possible changes of effect size.

**Table 1.** Sample size estimation per group for different effect size and power ( $\alpha = 0.05$ , 2-sided).

| effect size | power 70% | power 80% | power 90% |
|-------------|-----------|-----------|-----------|
| 0.6         | 34        | 43        | 58        |
| 0.55        | 40        | 52        | 70        |
| 0.50        | 49        | 63 | 84        |
| 0.45        | 61        | 78        | 103       |
| 0.40        | 77        | 98        | 131       |

In order to assess if the trial could be underpowered, a further probabilistic sensitivity analysis on the sample size and the power is carried out. This analysis puts uncertainty over the parameters  $\theta$  and  $\sigma^2$ . It is assumed that the prior mean of  $\theta$  is 6.25 with standard deviation 1, while for  $\sigma$  is assumed a prior mean of 12.5 and standard deviation of 1 (subject to the constraint of  $\sigma$  to be positive).

A Monte Carlo simulation method is applied to simulate values of  $\theta$  and  $\sigma^2$  from their prior distributions, substituting them into the sample-size formula and the resulted simulation values  $n_1^*, \dots, n_B^*$  recorded.

For a fixed  $n$ , the power is given by

$$power = \Phi(\sqrt{(n\theta/2\sigma^2)} + z_{0.025}).$$

If is decided to use 63 patients per group, values for the  $power$  can be simulated using the same methodology, resulting in simulated values  $power_1^* \dots power_B^*$ .

A total of  $B=10000$  simulated values  $n_b^*$  and  $power_b^*$  were carried out. Figure 1 gives the density estimation of these two quantities. They present a clear uncertainty for sample size and power values.

To achieve a fixed power of 80 % the median of the simulated sample size  $n^*$  is 88. For a fixed  $n=63$  the median of the simulated  $power^*$  values is 65%. These results indicates that the deterministic sample size calculation may give optimistic results and a larger sample size should be used to achieve a power of 80%.

Fixing  $n=88$  in the power formula and simulating again  $B=10000$  gives a median power of 79.6 %, which is more close to the trial power requirements. The recommended sample size for this trial is  $n=88$  per group.

**Figure 1.** *Left panel:* distribution for necessary sample size  $n$  to achieve 80% power. *Right panel:* power distribution with a fixed  $n = 63$  patients per group.

[figure not shown][figure not shown]

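### Section 9.2: the simulated medians behind 88 per group (88, 65%, 79.6%) do not follow from the priors stated for them, so priors and results must be reconciled

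*Protocol*

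**What the plan says.** Everything below is in Protocol section 9.2 unless another place is named.

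- **Deterministic step.** "A sample size of 63 in each group will have 80% power to detect an effect size of 0.50", with "a known common standard deviation of 12.5" and "using a two group normal test with a 0.05 two-sided significance level". The effect size of 0.50 "implies a clinically significant, large change of 6.25 in this measure of physical quality of life". Table 1 lists 63 per group for 80% power and 84 per group for 90% power at effect size 0.50.
- **Probabilistic step.** The prior mean of θ (the difference) "is 6.25 with standard deviation 1, while for" σ there "is assumed a prior mean of 12.5 and standard deviation of 1", with σ constrained to be positive. The family of the priors is not named. There are 10,000 draws.
- **Results.** The median size for 80% power is given as 88 per group, and the median power at 63 per group as 65%. Using 88 "gives a median power of 79.6 %, which is more close to the trial power requirements".
- **Inference.** "These results indicates that the deterministic sample size calculation may give optimistic results", and 88 per group is recommended. The Protocol Summary carries this forward as 2 × 88.

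**The concern.** Both priors are centred on the values used in the deterministic step, and both are narrow: an SD of 1 is 16% of 6.25 and 8% of 12.5. Required size falls, and power rises, as θ/σ rises. The median of each simulated quantity is therefore fixed by the median of θ/σ, which these priors leave at about 0.50. Adding uncertainty of this kind spreads the results out but hardly moves their medians. A shift in the median from 63 to 88 per group, and from 80% to 65% power, therefore cannot come from the stated inputs.

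The simulation is the only derivation that section 9.2 shows for 88 per group. If its inputs and outputs do not belong together, the power quoted for the confirmatory test cannot be relied on. A reader also cannot tell how much uncertainty, and about which quantity, the recommended size was meant to cover.

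**Working it through.** **Inputs (section 9.2).** z for 80% power = 0.84; z for two-sided 0.05 = 1.96; θ = 6.25; σ = 12.5; prior SD 1 for each. My assumption: independent normal priors, with σ truncated at 0.

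**Formulas.** n = 2σ²/θ² × (0.84 + 1.96)², and power = Φ(√(n/2) × θ/σ − 1.96). The second is the counterpart of the protocol's sample-size formula, with θ squared under the root.

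**1. Deterministic figures reproduce.**
- n = 2 × 7.84 / 0.25 = 62.7, so 63.
- Power at 63 = Φ(√31.5 × 0.5 − 1.96) = Φ(0.846) = 80.1%.
- Power at 88 = Φ(√44 × 0.5 − 1.96) = Φ(1.357) = 91.3%.

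The last value fits Table 1, where 84 per group gives 90%.

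**2. Simulation with the stated priors (2,000,000 draws).**

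| Quantity | Protocol (median) | Recomputed median | Recomputed mean |
|---|---|---|---|
| n per group for 80% power | 88 | 62.7 | 68.7 |
| Power at 63 per group | 65% | 80.1% | 77.9% |
| Power at 88 per group | 79.6% | 91.3% | 88.2% |

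Under these priors, 88 is roughly the 82nd percentile of the required size, not the median.

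**3. Simulation noise is not the cause.** Over 500 repeats of 10,000 draws, the medians ranged over 61.9–63.6 for n, 79.6–80.6% for power at 63 and 90.9–91.6% for power at 88.

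**4. The unnamed prior family is not the cause.** A gamma prior for σ, lognormal priors for both, or a prior placed on σ² give 62.6–63.9, 79.4–80.2% and 90.7–91.3%.

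**5. The printed power formula is not the cause.** As it appears, θ is not squared. Taken literally, it gives Φ(√(63 × 6.25/312.5) − 1.96) = Φ(1.122 − 1.96) = 20% at 63, and 26% at 88. The reported powers were not computed that way.

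**6. What the reported figures imply.** Solving each for θ/σ:
- from n = 88: √(15.68/88) = 0.422;
- from 65% at 63: (0.385 + 1.96)/√31.5 = 0.418;
- from 79.6% at 88: (0.827 + 1.96)/√44 = 0.420.

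The three agree, so they look like output of one simulation whose median θ/σ was about 0.42.

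**7. Inputs that would reproduce them.** At least two quite different changes do:

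| Priors | Median n | Power at 63 | Power at 88 |
|---|---|---|---|
| θ as stated; σ mean 12.5, SD 12, truncated at 0 | 88.1 | 65.8% | 79.9% |
| θ mean 5.25, SD 1; σ as stated | 89.0 | 65.4% | 79.5% |

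In the first row, truncation at 0 raises the median of σ to about 14.8, and 6.25/14.8 = 0.42.

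**The case against.** The strongest reply is that the outputs may be right and the printed inputs wrong. The three results agree with one another, which makes slips in the outputs unlikely. The positivity constraint on σ also has no effect at mean 12.5 and SD 1, because zero lies 12.5 SDs away; it matters only if the intended SD was much larger, and an SD near 12 does reproduce the figures. This stands as a plausible explanation, though not a proven one. For that reason the correction cannot simply replace the reported medians.

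A reader might infer that the trial was really planned for an effect of 0.42. The document does not support this. The Protocol Summary and section 9.2 both give 0.50, no section mentions 0.42, and a wide truncated prior for σ yields that median while the prior mean of θ remains 6.25.

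A reader might also infer that the remark about optimism is simply false. It is not quite. Under the stated priors, mean power at 63 is 77.9% and the mean required size is 68.7, so the direction holds for averages. It fails for the median, which is the measure the protocol uses, and the effect is far smaller than reported.

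The unsquared θ may be a lost superscript in the print or in the text extraction. It generated none of the reported results and adds no weight to the point.

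Finally, the discrepancy runs in the safe direction, and Protocol section 5.3 says that drop-out was considered in the sample size. That is fair, but section 9.2 contains no drop-out rate, so drop-out does not explain 88 as written.

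**Conclusion.** Section 9.2 is internally inconsistent. On its stated priors, the median required size is about 63 rather than 88, median power at 63 is about 80% rather than 65%, and median power at 88 is about 91% rather than 79.6%: a difference of nearly 12 percentage points in the power quoted for the recommended size. The recomputed values assume independent priors with the stated means and SDs, all patients evaluable, and the protocol's two-group normal test; they barely change across the prior families tried.

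Whether the priors or the results are misreported cannot be settled from the document. Nor does the error mean that the trial is too small. At effect size 0.50, 88 evaluable patients per group exceed the 80% target. With an assumed loss of 10% (79.2 evaluable), power is about 88%; with 28% (63.4 evaluable), about 80%. What fails is the stated justification for 88, not the number itself.

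**What to change.** Reconcile the priors with the results in section 9.2, by one of two routes.

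- **If the reported results are the intended ones:** state the priors actually used, including their family, centre and spread, say why they are reasonable, and keep 88, 65% and 79.6%.
- **If the stated priors are the intended ones:** re-run the simulation and report about 63 per group, 80% at 63 and 91% at 88, marked as fully evaluable. Reword the sentence on optimism so that it refers to mean power (77.9% at 63), and redraw Figure 1. Then give the actual basis for 88. One candidate is 63 evaluable plus an explicit drop-out allowance, which at 88 would be up to about 28% (1 − 63/88 = 0.284). The rate should be stated, since section 5.3 refers to it and section 9.2 omits it.

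On either route, print θ squared in the power formula.

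The cost is a rewrite of part of section 9.2 and, on the second route, of Figure 1. Enrolment of 176, the test and the significance level need not change.

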### 9.3.A demonstration of the potential for recruiting the required number of suitable subjects within the intended period

A pilot study was performed in all trial centres in November and/ or December 2004. All consecutive patients in the collaborating somatic departments were pre-screened and patients without evident reasons for exclusion (major organic disease, age ) were asked for their informed consent to take part in the pilot assessment and interview. Variations in rates of pre-screening exclusions are mostly due to different percentages of organically explained disorders in the different settings. Patients were given the SOMS-7 (see 5.9) and those above cut-off took part in an excerpt of the SCID-Interview to test for presence of Multisomatoform Disorder (MSD) and were checked for other inclusion and exclusion criteria as defined in 5.6. Eligible patients were informed about the planned study orally and with written material, afterwards they were asked whether they would agree to take part in this study if it became available.

| Trial Centre              | Weeks of screening | Number of assessed out of total patients seen (N) | Eligible patients w. MSD (N) | Patients agreeing to take part (N) |
|---------------------------|--------------------|---------------------------------------------------|------------------------------|------------------------------------|
| Heidelberg    | 3                  | 90 out of 120                                     | 17                           | 14 (19 per month)                  |
| Düsseldorf  | 3                  | 38 out of 52                                      | 8                            | 6 ( 9 per month)                   |
| Hannover      | 2                  | 10 out of 25                                      | 6                            | 6 ( 12 per month)                  |
| München       | 2                  | 20 out of 32                                      | 6                            | 4 ( 8 per month)                   |
| Münster     | 3                  | 11 out of 168                                     | 6                            | 6 ( 8 per month)                   |
| Regensburg  | 4                  | 26 out of 200                                     | 6                            | 6 ( 6 per month)                   |

Setting: Pain Centre; Internal Medicine; Neurology; Dental Medicine

Although the rates of eligible patients agreeing to take part are different between the centres, the results of this pilot study confirm that each centre will be able to fulfil the recruitment rate of approx. 4 eligible patients per centre per month agreeing to be randomized into the study.

### 9.4. Criteria for the termination of the trial

There are no formal statistical stopping rules defined for the trial. Premature study termination can be due to the following reasons:

- risk/ benefit ratio is changed
- DMSC recommends to stop the trial

Regular study termination will take place when the calculated numbers of patients in both arms have completed their follow-up.

### 9.5. Procedure for accounting for missing, unused, and spurious data according manuals

Missing data in the primary endpoint will be handled according to the manual of the SF-36.

### 9.6. Procedures for reporting any deviation(s) from the original statistical plan

Any deviations from the original statistical plan will be described and justified in protocol and in the final report, as appropriate.

### 9.7. Selection of subjects to be included in the analyses (e.g. intention-to-treat, all randomized subjects, all eligible subjects, evaluable subjects.)

The study population will be as follows:

- Intention- to- treat- population  
This population consists of all subjects randomised, irrespective of whether they received the

experimental or control intervention. Subjects will be analysed according to the intervention to which they have been randomised.

- Per- protocol population  
This population is the subset of all subjects included in the trial which excludes those subjects who had a major protocol deviation.

The efficacy analysis with primary and secondary endpoints criteria will be done in the intention-to- treat population.

In addition, for informative purposes, a less conservative analysis based on the per- protocol- population will be done for the primary and secondary endpoints.

Conclusions of the trial will be based only on the intention- to- treat population.

## **10. Direct Access to Source Data/Documents**

We ensure that it will be specified in written agreements that the investigators institutions will permit trial-related monitoring, audits, IRB/IEC review, and regulatory inspections, providing direct access to source data / documents.

## **11. Quality Control and Quality Assurance**

All efficacy parameters are derived from standardized and validated instruments.

All measures concerning monitoring/quality assurance will be conducted in accordance to ICH-GCP. Monitors are to be qualified by education, training, and experience.

### **11.1. Initiation Visit**

The monitor will give the investigator an extensive introduction to study protocol and study requirements. He/she is responsible for ensuring and documenting that each investigator clearly understands and accepts the responsibilities and obligations incurred in conducting a clinical study, for example how to obtain informed consent in accordance with GCP and the way of documenting adverse events.

### **11.2. Periodic Monitoring Visits**

The monitor will visit each site regularly. The number of visits is dependant on the number of subjects enrolled and the scope of the contractual obligations at each site. A maximum of 8 visits per site including initiation and termination visit is anticipated.

The following key variables will to be monitored to 100%:

- Inclusion criteria
- Exclusion criteria
- Informed consent
- Primary and secondary outcome variables

The monitoring of other parameters will be randomly specified.

Monitoring will be conducted according to the harmonized Standard Operating Procedures (SOPs) of the KKS-AG, study specific processes will be described in detail by working procedures.

Monitoring reports will be prepared for all visits. Reports must always include the following information:

- Date of the visit;
- List of study site personnel present;
- State of enrolment
- A summary of the findings, problems, and actions taken to correct any deficiencies.

### **11.3. Study termination visit**

All routine monitoring functions must be performed prior to the study termination visit; all queries generated by the data management should be answered. The monitor proves all study site documents to be complete and correct. He/she reminds the investigator of the obligation to retain the records according to regulatory requirements.

## **12. Ethics**

As it is based on common therapeutic strategies in patients with medically unexplained symptoms, the intervention in PISO is not experimental. Psychotherapeutic interventions like this have repeatedly been shown to be relatively safe, but all have potential side effects. In particular, there is a risk that during the intervention patients may transiently become more depressive and/ or suicidal as a sign of altered emotional processing of life stresses. Close monitoring of this risk by the therapist is assured through the treatment manual and is helped by the fact that the intervention is taking place not in group, but in single patient format. Appropriate action (e.g. antidepressive medication, psychiatric in-patient referral) is defined in a manual for clinical care that will be adapted to the local situation of each centre. This manual also defines the clinical care for drop outs.

The procedures protecting against bias and defining termination of the study, study site closure and patient withdrawal are laid down in the Trial Protocol; they also contribute to patients' safety.

Before deciding to take part in the trial, patients' informed consent will be obtained and legal and regulations of the ethics committees involved will be followed to assure patients' safety and confidentiality.

For the pilot trial assessing achievability of recruitment rate, the patient information and consent form for the study itself (and for the pilot trial) were checked and agreed upon by the ethics committee of the University Hospital Düsseldorf on Nov. 30th, 2004

### **12.1. Independent ethics committee**

The Coordinating Investigator will submit the final protocol and proposed Patient Information and Informed Consent documents to the Independent Ethics Committee (IEC), which is responsible for the Principal Investigators site. Copies of all these documents will be given to all Ethics Committees, which are responsible for other sites, participating in the study. The clinical trial will not be initiated until appropriate documentation of IEC approval of the study protocol and the Patient Information/Informed Consent has been received by all participating sites.

Modifications to the protocol will be submitted to the IEC for approval.

Potential modifications will be implemented only after IEC written approval of these changes has been received by the participating sites.

The Investigators will make appropriate and timely reports to the IEC as required by applicable government regulations and IEC policy. In addition to the progress reports, all known information regarding serious adverse events (SAE), whether observed at their clinical site or at another site participating in the clinical study, will be reported to the IEC.

It is the Investigators' obligation to provide the Coordinating Investigator with copies of all study-related correspondence with the IEC in a timely fashion and to retain original within an appropriate filing system.

### **12.2. Ethical conduct of the study**

#### **12.2.1 Regulatory requirements, guidelines and standards**

The trial will be performed according to ICH-GCP. Good Clinical Practice (GCP) is an international ethical and scientific quality standard for designing, conducting, recording and reporting trials that involve the participation of human subjects. Compliance with this standard provides public assurance that the rights, safety and well-being of trial subjects are protected,

consistent with the principles that have their origin in the Declaration of Helsinki, and that the clinical data are credible.

Declaration of Helsinki

The conduct of the trial is going to be in accordance with the declaration of Helsinki (2000, Edinburgh, Scotland).

### **12.2.2 Authority approvals and registration**

Requirements of Health Authorities and national regulations will be respected. The trial will be registered immediately in receipt of the notification of award by the BMBF/DFG at <http://www.controlled-trials.com>

### **12.3. Patient Information and Informed Consent**

Patient Information and Consent forms are to be approved by the responsible ethics committees and recruitment cannot commence before approval has been given.

Written informed consent must be obtained from all patients prior to the study inclusion. The patient and the investigator will sign the current IEC-approved version of the consent form and a signed copy of the consent form will be given to the patient. The data that consent was obtained will be recorded in the patient's medical record.

Original, signed consent forms must be made available to the study monitor when requested.

The potential risks and benefits of participation in this study are clearly identified in the patient consent form. Any patient eligible for participation in the investigation according to the inclusion will be advised of these potential risks and benefits before they sign the patient consent form and enrol in the study. Every patient has the right to refuse to participate in this investigation or to withdraw from the investigation at any time without any negative consequence.

A draft of the patient information and consent form is provided in Supplement 4.

